## Preterm birth

### Level 1: (highest level of certainty)

1. Certain LMP\* or intrauterine insemination (IUI) date or embryo transfer (ET) date with confirmatory 1st trimester scan (—————13 6/7 weeks).

OR

2. 1st trimester scan (—————13 6/7 weeks).

### Level 2A

1. Certain LMP\* with 2nd trimester scan (14 0/7 weeks to 27 6/7 weeks). If LMP and U/S do not correlate, default to U/S GA assessment.

OR

2. Certain LMP\* with 1st trimester physical examination.

### Level 2B

Uncertain LMP with 2nd trimester scan (14 0/7 weeks to 27 6/7 weeks).

### Level 3A

1. Certain LMP with 3rd trimester scan – 28 0/7 weeks +.

OR

2. Certain LMP with confirmatory 2nd trimester FH.

OR

3. Certain LMP with birth weight.

OR

4. Uncertain LMP with 1st trimester physical examination.

### Level 3B

1. Uncertain LMP with FH.

OR

2. Uncertain LMP with newborn physical assessment.

OR

3. Uncertain LMP with Birth weight.

## Small for gestational age

SGA (small for gestational age) definition: weight below 10th percentile for gestational age as assessed against a validated global, regional or local standard.

### Level 1 of diagnostic certainty

- Weight below 10th percentile for gestational age  
AND

---

 The case definition should be applied when there is no clear alternative diagnosis for the reported event to account for the combination of symptoms.

- The following used in assessment of weight:
  - o Newborn weighed within 24 h of birth
  - o Weight assessed using a calibrated electronic scale with 10 g resolution
 AND
- The following for assessment of gestational age:
  - o Certain LMP or IUI or embryo transfer date AND confirmatory ultrasound in first trimester
 OR
  - o First trimester ultrasound

#### Level 2A of diagnostic certainty

- Weight below 10th percentile for gestational age
- AND
- The following used in assessment of weight
  - o Newborn weighed within 24 h of birth on any scale with a <50 g resolution, tared to zero and calibrated
 AND
- The following for assessment of gestational age:
  - o Certain LMP with first or second trimester ultrasound
 OR
  - o Certain LMP with first trimester physical exam^3

#### Level 2B of diagnostic certainty

- Weight below 10th percentile for gestational age
- AND
- The following used in assessment of weight
  - o Newborn weighed within 24 h of birth on any scale with a <50 g resolution, tared to zero and calibrated
 AND
- The following assessment of gestational age
  - o Uncertain LMP with second trimester ultrasound

#### Level 3A of diagnostic certainty

- Weight below 10th percentile for gestational age
- AND
- The following used in assessment of weight
  - o Infant weighed within the first 48 h of life
  - o Newborn weighed on any scale with a <50 g resolution, tared to zero and calibrated
 AND

---

 If Physical exam and ultrasound do not correlate, default to ultrasound.

- The following assessment of gestational age
  - o Certain LMP with third trimester ultrasound
  - OR
  - o Certain LMP with confirmatory 2nd trimester fundal height
  - OR
  - o Certain LMP with birthweight
  - OR
  - o Uncertain LMP with first trimester physical exam

#### Level 3B of diagnostic certainty

- Weight below 10th percentile for gestational age
- AND
- The following used in assessment of weight
  - o Infant weighed within the first 48 h of life
  - o Newborn weight assessed by measuring the difference between an adult holding the infant and the adult being weighed alone on any scale
- AND
- The following assessment of gestational age
  - o Uncertain LMP with fundal height
  - OR
  - o Uncertain LMP with newborn physical assessment
  - OR
  - o Uncertain LMP with birthweight

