## **5.4 Exploratory study outcomes**

### **5.4.1 Missing elements to meet GAIA case definition**

To better understand why GAIA case definitions are not met, the type of data elements that are required by the GAIA case definition but that are missing will be described.

For each health outcome, the reasons why identified cases could not be classified will be tabulated (e.g. four identified cases of neonatal death could not be classified because date of death was unknown).

If feasible, reasons will be grouped, and proportions will be calculated.

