##### Level 2B of diagnostic certainty

1. Live birth, stillbirth, or spontaneous or therapeutic abortion of at least 24 weeks of GA~  
AND
2. HC 2 SD below mean or <3 percentile according to GA and gender, using appropriate standardized reference charts for the population (e.g., WHO growth reference charts if GA ≥37 weeks and Intergrowth-21st reference charts for GA 24–36 weeks)  
AND

3. Measured within the first 24 h § OR Measured >36 h and up to 6 weeks after birth or end of pregnancy with no apparent post-natal insult resulting in microcephaly

~GA assessed based on uncertain LMP with 2nd trimester US scan

§Take into account the variability in this period based on molding of the head

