#### Level 3 of diagnostic certainty

Newborn infant weighed on day 1 or 2 of life (first 48 h of life)

AND

Weight measured using dial/spring/color-coded scale

AND

Weight assessed as <2500 g

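### The SGA levels in Annex III are not nested: a calibrated-scale weight combined with uncertain LMP plus fundal height or birth weight meets no level, while a cruder weighing of the same infant meets Level 3B

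*Protocol*

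**What the plan says.** Annex III defines each SGA level by a weight criterion joined to a gestational-age criterion.

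- **Level 3A** asks for "Newborn weighed on any scale with a <50 g resolution, tared to zero and calibrated" within 48 h. Its only uncertain-LMP route is "Uncertain LMP with first trimester physical exam".
- **Level 2B** takes "Uncertain LMP with second trimester ultrasound" with a comparable scale, within 24 h.
- **Level 3B** asks for weighing within 48 h and "Newborn weight assessed by measuring the difference between an adult holding the infant and the adult being weighed alone on any scale". Its dating routes are "Uncertain LMP with fundal height", uncertain LMP with newborn physical assessment, and uncertain LMP with birth weight.

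Nothing in Annex III or section 4.10 says that a better weighing, dating or timing method also satisfies a lower level. Section 4.10 assigns classification to the Brighton Collaboration ABC tool and does not describe its logic.

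Section 5.2.2.1 makes applicability a primary outcome: classified cases divided by identified cases with a completed CRF, reported overall and by site, country, region and facility level. Section 5.3.2 compares applicability across categories of technical equipment and names type of scale as an example. For unclassified cases, section 5.4.1 plans that "the type of data elements that are required by the GAIA case definition but that are missing will be described".

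**The concern.** A graded definition is normally expected to be monotone: better evidence should give the same level or a better one. Here a better weight can move an infant from Level 3B to no level at all.

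Three analyses depend on this. In the primary proportion such an infant stays in the denominator and leaves the numerator. In 5.3.2 a site with good scales could look worse than one that weighs infants in an adult's arms, which is the opposite of what the comparison is meant to detect. Under objective 3.3.1 and section 5.4.1, failure to classify is explained by missing data elements, yet in these records every element is present and only the combination is absent.

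**Working it through.** **1. The plan's own precision figure.** Section 5.1.2, Table 1, with n = z²·p(1−p)/d², p = 0.50, d = 0.10 and z = 1.96 (the 95% level is inferred; that section does not state it): 1.96² × 0.25 / 0.01 = 96.04, rounded up to 97. This matches, so ±10 points per site and outcome is the yardstick used below.

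**2. SGA levels read literally.** Take an infant below the 10th percentile for gestational age. The first weighing column is a calibrated, tared 10 g electronic scale within 24 h. The second is adult-difference weighing within 48 h on a scale too coarse for Level 3A.

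| Dating | 10 g electronic scale | Adult-difference |
|---|---|---|
| First-trimester ultrasound | Level 1 | none |
| Uncertain LMP + second-trimester ultrasound | Level 2B | none |
| Uncertain LMP + first-trimester examination | Level 3A | none |
| Uncertain LMP + newborn examination | Level 4 at best | Level 3B |
| Uncertain LMP + fundal height | **none** | Level 3B |
| Uncertain LMP + birth weight | **none** | Level 3B |

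The two bold cells fail Levels 1, 2A, 2B and 3A on dating and Level 3B on weighing. They also fail Level 4. Its entries concern an infant with no actual weight, gestational age from infant examination only, or a coded or charted diagnosis without documented weight or gestational age. None of these describes an infant with a recorded weight and another dating method, whether the entries are read as alternatives or jointly. Level 5 is for infants without SGA.

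The last column shows the mirror gap: better dating with cruder weighing also meets no level.

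**3. Low birth weight.** Levels 1 and 2 require a calibrated scale, or a facility standard operating procedure (SOP) that meets the criteria. Level 3 has no calibration requirement but asks for "Weight measured using dial/spring/color-coded scale", and Level 4 needs a proxy measure. An infant weighed on an electronic scale of unknown calibration, at a facility whose SOP does not meet the criteria, therefore has no level. A colour-coded scale of unknown calibration reaches Level 3. The birth-weight CRF allows unknown as an answer on calibration.

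**4. Microcephaly.** Level 2B requires "GA assessed based on uncertain LMP with 2nd trimester US scan" and a head circumference measured within 24 h, or after 36 h and up to 6 weeks. A measurement at 24–36 h, which is the Level 1 window, misses 2B on timing, misses Levels 1 and 2A on dating, and misses 3A because 3A is for LMP without a confirmatory first- or second-trimester ultrasound. Levels 3B and 4 then need a coded diagnosis, or inspection without measurement. An uncoded case has no level.

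**5. Size.** Let g be the share of CRF-completed SGA cases in the gap. Then as-published applicability = nested applicability − g. The protocol gives no value for g, so the values below are assumptions, shown with n = 100 and an assumed nested applicability of 90%. Half-width = 1.96 × √(p(1−p)/100).

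| g (assumed) | As-published p | Half-width |
|---|---|---|
| 5% | 85% | ±7.0 points |
| 10% | 80% | ±7.8 points |
| 20% | 70% | ±9.0 points |
| 30% | 60% | ±9.6 points |

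The loss equals g whatever nested value is assumed. At g of about 10% it reaches the ±10 points planned per site.

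**The case against.** The strongest reply is that the GAIA definitions are themselves what is being tested. If a definition cannot place a well-measured infant, a low proportion is a correct finding about that definition, and rewriting the levels in section 4.10 would replace the instrument under study. This stands. It is why the as-published figure should remain primary. It does not answer the 5.4.1 problem, because a logic gap in a definition would still be described as a missing element.

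Second, the ABC tool's logic is not shown, and the Annex cannot be checked here against its source. This also stands and makes every consequence conditional.

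Third, the two weight lines in Level 3B carry no connector and might be read as alternatives, so that any weighing within 48 h would do. Level 1 uses the same layout, however, and on that reading any weighing within 24 h would satisfy it, leaving its scale requirement without effect.

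Fourth, the gestational-age CRF as shown records an LMP date or unknown and has no item on certainty of the LMP, so it is unclear which records would be treated as uncertain. For an infant on a calibrated scale dated by LMP with second-trimester fundal height, that judgement decides between Level 3A and no level. This is a reason to settle the rule, but it prevents any estimate of how many cases fall in the gap.

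Fifth, 5.4.1 also says that reasons for non-classification will be tabulated and grouped if feasible, which is wide enough to hold a reason of this kind. That is fair; the change needed there is small.

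**Conclusion.** The SGA levels as written in Annex III are not nested. The certain gap is two dating routes, uncertain LMP with fundal height and uncertain LMP with birth weight, when the infant is weighed on a calibrated scale. Similar gaps exist for low birth weight where calibration is unknown and the SOP route is not met, and for uncoded microcephaly with uncertain LMP plus second-trimester scan measured at 24–36 h.

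Two stronger readings are tempting and not supported. A reader might infer that every properly weighed SGA infant with an uncertain LMP is unclassifiable. That is wrong: second-trimester ultrasound and first-trimester examination are accepted on a suitable scale in the stated window, first-trimester ultrasound needs no LMP at Level 1 on a 10 g electronic scale within 24 h, and newborn-examination dating may fall to Level 4. A reader might also infer that primary SGA applicability is understated. That is not established: it depends on literal application by the tool, on such cases occurring, and on treating the published definition as something other than the object of measurement.

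What remains is a conditional effect of unknown size on the primary proportion, a possible distortion of the scale comparison in 5.3.2, and a likely misdescription under 5.4.1.

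**What to change.** - Confirm and document how the ABC tool handles these SGA, low-birth-weight and microcephaly combinations, including how it decides that an LMP is uncertain.
- Keep classification by the definitions as published as the primary applicability figure.
- Add a prespecified sensitivity figure in which a weighing, dating or timing method at least as good as the one listed satisfies that level. For SGA, a weight meeting Level 3A or better would satisfy the Level 3B weight criterion.
- In 5.4.1, tabulate cases with all elements present but no matching combination separately from cases with an element missing.
- Read the 5.3.2 comparison by type of scale under both figures.

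The cost is analysis wording and a second column in the affected tables. The CRF already records scale type, graduation, calibration and adult-difference weighing, so the sensitivity figure needs no new data. The downside is two applicability figures for the affected outcomes, which must be labelled so that the as-published one is clearly primary.

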#### Level 4 of diagnostic certainty

- Baby noted to be small, but no actual weight
- Baby with GA assessed only by infant examination
- Diagnosis extracted from billing codes or chart, with no documentation of actual birth weight or GA

#### Level 5 of diagnostic certainty

- No evidence of SGA or a confirmed diagnosis other than SGA

### Stillbirth

#### *Antepartum stillbirth*

Fetal death occurs prior to the evidence of labor.

#### Level 1

- Delivery of an infant with no of signs of life at birth (No spontaneous movements, no umbilical cord pulse, no heartbeat, no respirations, Apgar score of 0 at 1 and 5 min) determined by physical examination after delivery (with or without electronic monitoring of heart rate, respiratory

rate, and pulse oximetry).

AND

- Prenatal ultrasound examination documenting lack of fetal cardiac activity or movement before the onset of labor.

OR

- Auscultation for fetal heart tones (using electronic devices or non-electronic devices) documenting lack of fetal heartbeat.

AND

- Maternal report of lack of fetal movement for 24 h or more.

OR

- Maternal physical examination confirming lack of fetal movement.

OR

- Radiology findings consistent with intrauterine fetal death.

AND

- Attended delivery followed by fetal physical examination after birth consistent with antepartum death, by obstetrician, neonatologist, pediatrician, maternal-fetal medicine specialist, or pathologist. In the setting where access to a specialist is not feasible, diagnosis by a health care provider trained or experienced to make the diagnosis is acceptable (e.g. general practice physician, mid-wife, nurse practitioner, a physician's assistant or other qualified trained practitioner).

OR

- Fetal/placental pathology report consistent with antepartum death.

AND

- Gestational age within pre-defined range for selected stillbirth definition as assessed by maternal and/or fetal parameters (Level 1 or 2 in GA assessment algorithm).

## Level 2

- Delivery of an infant with no of signs of life at birth (No spontaneous movements, no umbilical cord pulse, no heartbeat, no respirations, Apgar score of 0 at 1 and 5 min) determined physical examination after delivery.

AND

- Maternal report of lack of fetal movement for 24 h or more.

OR

- Maternal physical examination confirming lack of fetal movement.

OR

- Auscultation for fetal heart tones (using electronic or nonelectronic devices) documenting lack of fetal heartbeat.

AND

- Attended delivery followed by physical examination after birth consistent with antepartum death, by specialist or qualified trained practitioner

appropriate to the health care setting.

OR

- Fetal/placental pathology report consistent with antepartum death.

AND

- Gestational age within pre-defined range for selected stillbirth definition as assessed by maternal and/or fetal parameters (Level 1–2 in GA assessment algorithm).

### Level 3

- Delivery of an infant reported to have no of signs of life at birth (No spontaneous movements, no umbilical cord pulse, no heartbeat, no cry or spontaneous respirations, no chest movement, and whole body cyanosis).

AND

- Maternal report of lack of fetal movement for 24 h or more prior to delivery.

OR

- Report of auscultation for fetal heart tones (using electronic or non-electronic devices) documenting lack of fetal heartbeat.

AND

- Non-attended delivery followed by physical examination of the fetus after birth consistent with antepartum death by a health care professional appropriate to the level of standard of care in the health care setting.

OR

- Verbal history by a trained health care provider, non-medical witness or the mother of a fetus born with no signs of life or unresponsive to resuscitation efforts immediately after birth and with physical features consistent with antepartum death.

AND

- Gestational age within pre-defined range for selected stillbirth definition as assessed by maternal and/or fetal parameters (Level 2–3 in GA assessment algorithm).

### Level 4

- Report of stillbirth but fetus is not available for physical examination after birth (no objective assessment can be made).
- Maternal information insufficient to assess gestational age.

## *Intrapartum stillbirth*

Fetal death occurs during labor and before delivery

### Level 1

- Delivery of an infant with no of signs of life at birth, including: No spontaneous movements, no umbilical cord pulse, no heartbeat, no

respirations, and Apgar score of 0 at 1 and 5 min.

- Determination of the absence of signs of life is made by physical examination after delivery, with or without electronic monitoring of heart rate, respiratory rate, and pulse oximetry.

AND

- Evidence of live fetus prior to onset of labor (documentation of fetal movement and of fetal heart tones by ultrasound prior to onset of labor) (Note: in the absence of evidence of a live fetus prior to the onset of labor, the fetal death should be reported as a stillbirth or an antepartum stillbirth).

AND

- Attended delivery followed by physical examination after birth consistent with intrapartum death by obstetrician, neonatologist, pediatrician, maternal-fetal medicine specialist, pathologist. In the setting where access to a specialist is not feasible, diagnosis by a health care provider trained or experienced to make the diagnosis is acceptable (e.g. general practice physician, mid-wife, or other qualified trained practitioner).

AND

- Gestational age within pre-defined range for selected stillbirth definition as assessed by maternal and/or fetal-neonatal parameters (Level 1 in GA assessment algorithm)

## Level 2

- Delivery of an infant with no of signs of life at birth, including: No spontaneous movements, no umbilical cord pulse, no heartbeat, no respirations, and Apgar score of 0 at 1 and 5 min.

- Determination of the absence of signs of life is made by physical examination after delivery, with or without electronic monitoring of heart rate, respiratory rate, and pulse oximetry OR documentation of lack of response to resuscitation efforts.

AND

- Evidence of live fetus prior to onset of labor (maternal report of fetal movement prior to onset of labor and documentation of fetal heart tones by auscultation or hand held Doppler) (Note: in the absence of evidence of a live fetus prior to the onset of labor, the fetal death should be reported as a stillbirth or an antepartum stillbirth).

AND

- Attended delivery followed by physical examination after birth consistent with intrapartum death by a health care professional appropriate to the level of standard of care in the health care setting.

AND

- Gestational age within pre-defined range for selected stillbirth definition as assessed by maternal and/or fetal parameters (Level 1–2 in GA assessment algorithm).

### Level 3

- Delivery of an infant reported to have no of signs of life at birth, including: No spontaneous movements, no umbilical cord pulse, no heartbeat, no cry, no spontaneous respirations or chest movement, and whole body cyanosis.

AND

- Evidence of live fetus prior to onset of labor (maternal report of fetal movement prior to onset of labor OR auscultation of fetal heart tones) (Note: in the absence of evidence of a live fetus prior to the onset of labor, the fetal death should be reported as a stillbirth or an antepartum stillbirth).

AND

- Non-attended delivery followed by physical examination of the fetus after birth consistent with intrapartum death by a health care professional appropriate to the level of standard of care in the health care setting OR verbal history by a trained health care provider, non-medical witness or the mother of a fetus born with no signs of life or unresponsive to resuscitation efforts immediately after birth.

AND

- Gestational age within pre-defined range for selected stillbirth definition as assessed by maternal and/or fetal parameters (Level 2–3 in GA assessment algorithm).

### Level 4

- Report of stillbirth but fetus is not available for physical examination after birth (no objective assessment can be made).

- Maternal information insufficient to assess gestational age.

## **Maternal immunization**

### Level 1 of diagnostic certainty

1. Woman confirmed as pregnant by positive pregnancy test or ultrasound confirmation

AND

2. Date/time of immunization of pregnant woman recorded in medical records by health care worker who administered/witnessed administration of vaccine

AND

3. Details of vaccine, including lot number, date of immunization

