### Level 2 of diagnostic certainty

1. Woman confirmed as pregnant by cessation of menstrual period and gravid uterus

AND

2. Date (at least month and year) of immunization of pregnant woman recorded in medical records by health care worker who administered/witnessed administration of vaccine

AND

3. Details of disease against which vaccinated

Level 3 of diagnostic certainty

1. Woman/medical attendant reports pregnancy AND

2. Woman reports receipt of vaccination during pregnancy, but no formal recording of immunization available.

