### Maternal immunization

| QUESTION                                                                                  |                                                                                                                                                                                    | ANSWERS                                  |
|-------------------------------------------------------------------------------------------|------------------------------------------------------------------------------------------------------------------------------------------------------------------------------------|------------------------------------------|
| 1                                                                                         | What is the date of LMP ?
(if 'unknown', skip all questions on 30 days before LMP)                                                                                              | Please enter DDMMYYYY or unknown. |
| 2a                                                                                        | Did the mother receive any vaccination during pregnancy?
Please only answer 'no' if there is documented evidence of no immunization; else please answer 'unknown'.       | Yes
No
Unknown                     |
| 2b                                                                                        | Did the mother receive any vaccination in the 30 days before LMP? Please only answer 'no' if there is documented evidence of no immunization; else please answer 'unknown'. | Yes
No
Unknown                     |
| (If the answer to both question above is 'no' or 'unknown', end of questionnaire.) |                                                                                                                                                                                    |                                          |
| 3                                                                                         | How many vaccine doses were administered during pregnancy in total?                                                                                                                | 1
2
3
4
>4
Unknown        |

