| Fill in the questions below for each dose administered during pregnancy                   |                                                                                                                                                                                    |                                          |

|                                                                          |                                                                                                                      |                                                                                                                                           |
|--------------------------------------------------------------------------|----------------------------------------------------------------------------------------------------------------------|-------------------------------------------------------------------------------------------------------------------------------------------|
| Dose during pregnancy                                      |                                                                                                                      |                                                                                                                                           |
| 4                                                                        | Against which disease was the mother immunized?                                                                      | Tetanus
Influenza
Pertussis
Other, please specify                                                                                |
| 5                                                                        | Was vaccination status obtained from medical records or reported by the mother?                                      | Medical records (e.g. ANC card, vaccination card, vaccine registry, etc.)
Reported by mother but no formal recording
Unknown        |
| 6                                                                        | What is the date of immunization of the pregnant woman?                                                              | Please enter DDMMYYYY or unknown.                                                                                                  |

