| 7                                                                        | What is the time of immunization of the pregnant woman?                                                              | Please enter the time or unknown.                                                                                                  |
| 8                                                                        | Was the date recorded in medical records by health care worker who administered/witnessed administration of vaccine? | Yes
No
Unknown                                                                                                                      |
| 9                                                                        | What is the name of the vaccine?                                                                                     | Adacel
Boostrix
Daptacel
Infanrix
Kinrix
Pediatrix
Pentacel
Quadracel
Tenivac
Other, please specify
Unknown |
| 10                                                                       | What is the manufacturer?                                                                                            | GlaxoSmithKline
Sanofi Pasteur
Other, please specify
Unknown                                                                     |
| 11                                                                       | What is the lot number?                                                                                              | Please enter your answer in free text.                                                                                             |
| OPTION TO 'ADD DOSE DURING PREGNANCY' AND REPEAT QUESTIONS |                                                                                                                      |                                                                                                                                           |
| 12                                                                       | How many vaccine doses were administered in the 30 days before LMP?                                                  | Please select your answer from the list.
Fill in the questions below for each dose administered in the 30 days before LMP       |

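### The maternal immunisation form does not record how pregnancy was confirmed, so for some mothers Level 1 cannot be established or told apart from Level 2

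*Protocol*

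**What the plan says.** Annex III (Maternal immunization) gives three levels, and each begins with a condition on the pregnancy itself.

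- **Level 1:** "Woman confirmed as pregnant by positive pregnancy test or ultrasound confirmation", a date or time of immunisation entered by the health worker who gave or witnessed the dose, and "Details of vaccine, including lot number, date of immunization".
- **Level 2:** "Woman confirmed as pregnant by cessation of menstrual period and gravid uterus", a date entered in the same way, and the disease vaccinated against.
- **Level 3:** "Woman/medical attendant reports pregnancy", and "Woman reports receipt of vaccination during pregnancy, but no formal recording of immunization available".

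The maternal immunisation form in Annex V asks for the LMP date and then "Did the mother receive any vaccination during pregnancy". For each dose it asks the disease, the source (one option is "Reported by mother but no formal recording"), the date and time, "Was the date recorded in medical records by health care worker who administered/witnessed administration of vaccine", the vaccine, the manufacturer and the lot number.

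Section 5.2.2.2 makes the proportion of vaccinated mothers who can be classified part of primary outcome 2. Section 5.3.1.2 reports the distribution over levels as a secondary outcome. Section 4.10 assigns levels with the Brighton ABC tool, and section 4.9 links mother and child forms by one identifier.

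**The concern.** The form covers the vaccination criteria of Levels 1 and 2 well but leaves out their first criterion. A classification needs some source for it, and the protocol names none. If criterion 1 counts as unmet whenever it was not recorded, a mother with a dated, health-worker-entered dose and a lot number can fail Levels 1 and 2. She is then shut out of Level 3 because she has a formal record. If criterion 1 is skipped, Level 1 is awarded on date and lot number alone, and women confirmed only clinically are graded too high.

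The study exists to learn whether sites can apply these definitions. A gap in the form could therefore be read as a weakness, or a strength, of a site's records. Whether Level 1 is reachable would also depend on which outcome the infant had, which has nothing to do with vaccine documentation.

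**Working it through.** No figure in the plan bears on this, so the check sets the criteria against the forms.

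**Step 1. Where evidence on criterion 1 is collected (Annex V).**

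- Pregnancy test: on no form.
- Ultrasound: gestational age reference form, items 7 to 10.
- Enlarged uterus on first-trimester examination: same form, item 11c.
- Second-trimester fundal height: same form, item 12.
- LMP date: maternal immunisation form and gestational age form.
- The general information form records gestational age in weeks and days but not how it was established.

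**Step 2. Which outcome forms call the gestational age form.** There are nine outcome forms for seven outcomes, because neonatal infection has three. Five call it: preterm birth, neonatal death, stillbirth, small for gestational age and microcephaly. The other 9 − 5 = 4 do not: low birth weight, bloodstream infection, respiratory infection and meningitis. The low birth weight form carries a heading on gestational age but refers only to the birth weight form, which has no item on pregnancy confirmation.

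**Step 3. Skip pattern.** Once a first- or second-trimester scan is dated (items 8d and 9d), the gestational age form ends. The uterus and fundal-height items are then never asked.

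**Step 4. Literal classification.** Assumptions: the dose date was entered by the health worker and the disease is known; an LMP date stands for cessation of menses; an enlarged uterus or a fundal height stands for a gravid uterus; pregnancy is taken as reported for Level 3.

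| Evidence available | Record with lot number | Record, no lot number | No record, mother's report |
|---|---|---|---|
| Maternal form alone | none | none | Level 3 |
| + GA form: early scan dated, form ends | Level 1 | none | Level 3 |
| + GA form: third-trimester scan and fundal height | Level 1 | Level 2 | Level 3 |
| + GA form: no scan, LMP and enlarged uterus or fundal height | Level 2 | Level 2 | Level 3 |
| + GA form: no scan, LMP only | none | none | Level 3 |
| GA form not completed | none | none | Level 3 |

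**Step 5. Accept delivery at the site as meeting criterion 1 of Level 2.** Every 'none' in the two record columns becomes Level 2. The primary proportion then no longer depends on the missing item. What stays lost is Level 1 in two groups: mothers without a gestational age form, and mothers confirmed by pregnancy test and not scanned.

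**The case against.** A reader might infer that mothers with a formal vaccination record can generally reach no level while those without one reach Level 3, so that the primary result is turned upside down. The documents do not support that, for three reasons.

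- The gestational age form is linked and is called for five of the seven outcomes. It gives Level 1 or 2 for many mothers with a record.
- The inversion relies on an uneven reading. The reported-pregnancy condition of Level 3 has no item of its own on the maternal form either, so pregnancy is being taken as given for Level 3 and as unproven for Level 2.
- Eligibility requires delivery at the site (section 4.3). A woman who delivered there was plainly pregnant, so criterion 1 of Level 2 can reasonably be inferred.

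It is also fair to say that many low birth weight infants will be preterm or small for gestational age and so may have a gestational age form anyway. The choice of fields that feed each criterion may also be laid down in an SAP or in the ABC tool, neither of which is at hand.

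These arguments largely protect the primary proportion, provided the inference from delivery is actually adopted. They do not close the gap at Level 1. A derivation rule cannot recover a pregnancy test that no form records, or an ultrasound on a form that was not completed. Section 5.5 rules out imputation.

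**Conclusion.** The point holds as a gap in data collection. Criterion 1 of Levels 1 and 2 is not on the maternal immunisation form, no form records a pregnancy test, and the only form with related evidence is not called for two of the seven outcomes. For the mothers concerned, Level 1 cannot be established or separated from Level 2, so section 5.3.1.2 is affected directly. The primary proportion in section 5.2.2.2 is at risk only under a strictly literal reading. That risk remains because the protocol does not say which reading applies.

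The size cannot be computed. The documents do not give the share of vaccinated mothers with a formal record, the share of cases with only a low birth weight or infection form, or the share confirmed by test alone. Any percentage would simply restate an assumed share. The correction is worth making because it is cheap and concerns a primary and a secondary outcome. It does not call the design into question.

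**What to change.** Add one item to the maternal immunisation form and use it for criterion 1: *Pregnancy confirmed by: pregnancy test / ultrasound / cessation of menses and gravid uterus / report only / unknown (all that apply).*

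For mothers already entered, state in section 5.2.2.2 that criterion 1 is taken from the linked gestational age form where it exists. Where that form is absent or does not settle the matter, delivery at the site is accepted as meeting criterion 1 of Level 2 but not of Level 1.

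The cost is one extra item, answerable from the antenatal records that section 4.8 already lists as a source, with the matching change to the electronic form and its documentation as an amendment under section 8.8. The drawback is that some mothers entered earlier are capped at Level 2 although their pregnancy may have been confirmed by test or scan. The report should say so when it presents the level distribution.
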